### Objectives

The aim is to evaluate the acceptability, feasibility and potential effects of a digital and nurse-led support intervention in primary care for patients with breast or prostate cancer during the first year after primary treatment.

## Methods

The protocol is prepared according to the SPIRIT 2013 statement^29^ and adapted with items from the CONSORT 2010 statement^30^ based on a guide to the reporting of protocols of pilot and feasibility trials.^31^ The SPIRIT schedule of enrolment, intervention and assessments is employed (table 1).

**Table 1 T1:** The SPIRIT schedule of enrolment, intervention and assessments

Timepoint	Enrolment	Allocation		Post-allocation			
	-*t*_1_	0	3 months	6 months	12 months	18 months	24 months
Enrolment:							
Eligibility screen	X						
Invitation letter	X						
Informed consent	X						
Allocation to intervention or control group		X					
Intervention: Reporting in Interaktor and health dialogues							
Breast cancer cohort							
Prostate cancer cohort							
Assessments:							
Demographic and medical data		X					
Primary outcomes				X			
Secondary outcomes		X	X	X	X	X	X

### Patient and public involvement

The intervention tested in these trials was developed in response to our previous research showing that patients treated for breast or prostate cancer have extended needs of support from the healthcare providers beyond the completion of treatment.^14 15^ The technique for ePRO and digital support is a system (Interaktor) including an app and a web interface. Interaktor was developed in cooperation with patients and healthcare professionals through interviews. For this follow-up project after cancer treatment, the app has been tested in a small sample of patients with feedback that has guided refinements before the final model.

### Study design

The study design is underpinned by the Medical Research Council (MRC) framework for complex interventions.^32^ These studies have cluster randomised controlled pilot trial design including patients with breast and prostate cancer, respectively, during the first year after ending primary treatment. The two pilot RCTs will be performed in PCCs in Region Stockholm. The studies have two parallel arms: the intervention plus standard care (intervention group) and standard care alone (control group). The intervention involves an entire PCC, and cluster randomisation is used to avoid the spill-over effect.^33^ To achieve representativeness for the cluster randomisation, the Care Need Index (CNI) for calculating economic compensation to the PCC is used.^34^ CNI measures healthcare needs for the distribution of primary care resources to populations with the biggest need. A high CNI equals low socioeconomic status, and a low CNI equals high socioeconomic status. Ten PCCs in the region were considered sufficient as a basis for our sampling. Five pairs of PCC were matched to the CNI and the size of the PCC regarding a number of allocated patients. Subsequently, a randomisation through sealed envelopes allocated the PCC to either intervention or control in each pair.

### Participants

#### Enrolment

The recruitment and participant enrolment were started in October 2023 and is expected to continue until January 2026. Patients diagnosed with breast or prostate cancer and who have ended primary treatment are identified through the database at the Stockholm Centre for Health Data on healthcare consumption by combining PCC individual identification codes and relevant ICD-10 codes. Criteria for inclusion are completed primary treatment with curative intent for breast or prostate cancer within the past 6 months, >18 years and able to speak and understand Swedish. The criterion for exclusion is cognitive impairment. The plan is that the intervention can be given during the first year after primary treatment and that the intervention period of 6 months falls within the frame of the first year. Eligible patients in the intervention PCC and the control PCC are consecutively recruited by an invitation letter prepared by the researchers and posted from the PCC. Patients who agree to participate return an informed consent form directly to the researchers (online supplemental material). A reminder is sent within 2 weeks to those who have not been heard from. The patients are then contacted by the researcher who estimates the possibility of inclusion with regard to the inclusion criteria.

### Standard care in the study region

After treatment for breast or prostate cancer, all patients have scheduled visits to the oncological clinics for regular follow-ups according to guidelines for respective diagnoses. For breast cancer, annual follow-ups are usual for at least 5 years and include mammography and in many cases endocrine therapy.^35^ For prostate cancer, follow-up is carried out at 3 or 6 months during the first year and includes a PSA test.^36^

All patients with breast or prostate cancer should be offered a coordination contact nurse at the oncological clinic to call when needed.^37^ The purpose is to improve information and communication between the patient and healthcare service and strengthen the patient participation in care. In Sweden, the basic health and medical care for most common conditions and illnesses is generally referred to as primary care.

Primary care has no specific role in caring for patients in the follow-up of cancer treatment. Patient contact with primary care occurs on the patients’ initiative when seeking care for any health concerns.

### Intervention

#### Intervention delivery

The intervention is intended for a 6 month period and consists of patients using an app for symptom reporting and self-care advice, together with supportive health dialogues with a study nurse at the intervention PCC (figure 1). The nurse is employed at the PCC and experienced in working within the primary care setting. The nurse receives a preintervention audio-recorded tutorial regarding symptoms and rehabilitation measures to assess for each diagnosis. Patients are expected to report symptoms regularly on a weekly basis or as agreed with the nurse. The nurse logs on to the web interface to view the reports before the patient’s visits. A study folder at each PCC provides information and flowcharts of the study process, consent forms, checklists for health dialogues and handbooks for patients and nurses, as well as a knowledge base and self-care advice. The nurses will have continuous contact with the researchers and access to technical support.

**Figure 1 F1:**
[figure not shown]
Illustration of the intervention.

#### Digital nurse-led support

Interaktor is a digital system for symptom management used in our previous studies during treatment for cancer.^38^,^40^ The system includes (a) an app that is downloaded to the patient’s phone or tablet where they report symptoms, view the reports in graphs and have access to a knowledge base and self-care strategies and (b) a web interface for the nurse to monitor the incoming reports, available in real-time. The content of the app is based on literature reviews, interviews with patients and healthcare professionals and national guidelines for each diagnosis. In this study, the patients in the breast cancer group report joint pain, discomfort in the breast, numbness/tingling in hands and feet, hot flushes, dry mucous membranes, fatigue, sleeping difficulties, depression, worry, concentration and memory, appetite and sexual health. The prostate cancer group reports on bladder function (difficulties urinating, leakage, urine urgency, blood in urine), bowel function (loose stool/leakage, constipation, flatulence, blood in stool), swelling/lymphoedema, pain, hot flushes, fatigue, sleeping difficulties, depression, worry, appetite and sexual health. If the patient answers yes to experiencing a symptom, there is a follow-up question about the frequency of the symptom—not often, sometimes, rather often or very often—followed by their rating of the distress of the symptom—not distressing, a little distressing, rather distressing or very distressing. The question concerning appetite is only assessed by the level of distress, and the question about sexual health is assessed on occurrence, allowing for commentary. Before sending in the report, the patients can write a free-text message. The app has an alert function where specific symptoms are set to generate an alert based on a risk assessment model. Alerts are triggered when patients answer that the symptoms occur *very often* and are *very distressing*. In the prostate cancer app, alerts can be triggered for pain, blood in stool, blood in urine and loss of appetite. In the breast cancer app, the reported symptoms are not considered acute and alerts are not generated. The triggered alerts send a notification to the nurse who is expected to contact the patient within 24 hours (during weekdays). The patients have continuous access to evidence-based self-care and lifestyle advice related to disease-specific symptoms. In connection with reporting the presence of a symptom, a notification shows the patient related self-care advice. These recommendations and general information about treatment and side effects (ie, what has caused them and how the symptom is experienced) can be retrieved in the knowledge base in the app. The recommendations for self-care and which symptoms should promote contact with a healthcare professional are the same as those provided through healthcare guidelines. Furthermore, reliable information can be retrieved through external links to relevant web pages or videos. Both the app and the web interface have a display of graphs to view the history of symptom reporting. Push notifications in the app will serve as reminders to report.

The reports made by the patients will be used in health dialogues, which are proposed to engage and support patients in self-care. Within a month after study inclusion, the nurse at the PCC books a meeting with the patient for a first dialogue. At this appointment, the nurse introduces the app and instructs the patients in the reporting procedure. The following health dialogue takes place in agreement between the patient and the nurse either as telephone calls, video conversations or face-to-face meetings. If needed, additional actions such as support from a physiotherapist, social worker, dietician or physician can be planned.

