### Outcomes

#### Acceptability and feasibility

To assess acceptability and feasibility, the participants in the intervention group and the study nurses will be interviewed about their experience of using Interaktor and the health dialogues. Furthermore, field notes with reflections from the health dialogues will be taken by study nurses. Objective measures will be extracted from the logged data in the app, that is, the number of reports (adherence) and self-care advice viewings. After the intervention has ended (at 6 months), the patients are surveyed via a questionnaire including the Acceptability E-scale^41^ and two selected items from the System Usability Scale.^42^ The composed questionnaire assesses ease of use, understandability, enjoyability, helpfulness, time required and overall satisfaction. To evaluate the feasibility of a future trial methodology, enrolment, recruitment and withdrawal rates will be documented. Other feasibility measures include completion rates and missing data in each study questionnaire.

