### Sample size

We adopted a sample size calculation for pilot randomised trials using a CI approach.^51^ To evaluate the potential effect of the intervention as compared with the control, and assuming a medium standardised effect size (0.5), 12 participants are required in each group with 80% one-sided CI. The question ‘overall satisfaction with the system’ in the Acceptability E-scale was chosen as a primary measure of acceptability for the sample size calculation. Aiming for the intervention to be acceptable to 70% of the participants with 20% precision (at least 50% were satisfied to use the intervention), 18 participants are required in the intervention arm. With an estimation of a 10% dropout, the total sample size of 20 participants in each study arm for each respective study group was considered appropriate.

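### The only stated alert trigger cannot be met for loss of appetite, one of the four alerting symptoms in the prostate app

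*Protocol article*

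**What the plan says.** All the relevant text is in the protocol article, section Digital nurse-led support.

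- **Item structure.** A patient who reports a symptom is asked how often it occurs and then how distressing it is, each on four levels. Two items are exceptions. Sexual health is recorded by occurrence, with room for comment. For appetite, "The question concerning appetite is only assessed by the level of distress".
- **Alert rule.** "The app has an alert function where specific symptoms are set to generate an alert based on a risk assessment model". The next sentence gives the trigger: "Alerts are triggered when patients answer that the symptoms occur *very often* and are *very distressing". It makes no exception for any symptom.
- **Alerting symptoms.** "In the prostate cancer app, alerts can be triggered for pain, blood in stool, blood in urine and loss of appetite". The breast cancer app generates no alerts.
- **Response.** An alert notifies the nurse, who should then contact the patient within 24 hours on weekdays. Separately, the system has "a web interface for the nurse to monitor the incoming reports, available in real-time".

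**The concern.** The rule joins two conditions, and one of them asks for an answer that the appetite item does not collect. Read literally, an appetite alert could never fire, although the sponsor chose loss of appetite as one of only four alerting symptoms.

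At stake is a safety-related part of the intervention. The alert is the only notification described that starts nurse contact within a fixed time. Real-time access to the reports is a partial substitute: under Intervention delivery, the nurse is described as logging on before the patient's visits, and the timing of dialogues after the first is left to agreement between patient and nurse. As described, nothing else obliges a nurse to look at a severe appetite report between visits.

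The description also matters beyond this study. The Discussion says that the work is meant to inform a larger definitive trial. Someone checking or reproducing the alert function from this text would find either no usable appetite threshold or one that cannot be met.

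**Working it through.** The plan gives no figure to reproduce. The check compares the trigger with the answers available for each alerting symptom.

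**Inputs**, all from Digital nurse-led support:

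1. Trigger: frequency is *very often* AND distress is *very distressing*.
2. Default item: frequency and distress are both asked.
3. Exceptions to the default: appetite (distress only) and sexual health (occurrence only).
4. Alerting symptoms in the prostate app: pain, blood in stool, blood in urine, loss of appetite.

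**Comparison**

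| Alerting symptom | Frequency asked | Distress asked | Trigger can be met as written |
|---|---|---|---|
| Pain | yes | yes | yes |
| Blood in stool | yes | yes | yes |
| Blood in urine | yes | yes | yes |
| Loss of appetite | no | yes | no |

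The rule fits 3 of the 4 listed symptoms and fails for 1 of 4.

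**Could the mismatch be only apparent?**

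- *A second appetite item.* The prostate symptom list has a single appetite entry, so loss of appetite does not point to a separate two-part question.
- *A separate threshold elsewhere.* The article gives none. The only related text is the reference to a risk assessment model, which is not described.
- *The other exception.* Sexual health lacks both ratings but is not an alerting symptom, so it raises no conflict.
- *The breast cancer app.* It also asks about appetite, but it generates no alerts and is not affected.

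**Does anything downstream depend on the rule?** Under Acceptability and feasibility, "Objective measures will be extracted from the logged data in the app, that is, the number of reports (adherence) and self-care advice viewings". Neither of these two logged measures counts alerts. The sample size rests on an assumed standardised effect and on overall satisfaction in the Acceptability E-scale, and the analysis section does not mention alerts. No outcome, sample size or analysis changes.

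**The case against.** The strongest reply is that this is one over-general summary sentence. The appetite exception stands three sentences before the trigger, and loss of appetite is then named as alerting. A sensible reader would apply the frequency condition only where frequency is asked and let appetite alert on distress. Thresholds for each symptom are configuration detail that an article may leave to the risk assessment model, or to the flowcharts and handbooks held at each centre. The app already exists, was used in earlier studies and was tested in a small sample before the final model, so nobody in this trial need configure it from this paragraph. Other safeguards are described: real-time reports, free-text messages, advice in the app on when to contact a professional, and continuing standard care.

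Much of this stands. It rules out the stronger inference a reader might draw, that the app fails to send appetite alerts or that patients have gone without contact. The documents do not show how the software is set, and a misworded rule is likelier than a faulty alert. Nor can the documents tell us how often an appetite alert would arise, so it would be wrong to treat the whole prostate intervention arm as affected.

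The reply does not rescue the sentence itself. The article did not leave the trigger to other material. It stated the trigger, the item structure and the list of symptoms, and the three conflict for appetite. The charitable reading also still leaves open which level of distress sets off the alert.

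**Conclusion.** The concern holds as an error in a stated rule. The only trigger given cannot be met for loss of appetite, and no other threshold is given for it. This follows from the text alone, assuming that pain, blood in stool and blood in urine follow the default item structure, as the description implies.

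The consequence is minor. It could reach only patients in the prostate intervention arm who report severe appetite distress, and it would affect their care only if the software followed the wording literally, which the documents do not establish. The statistical content of the plan is untouched. The point still merits action because the rule concerns patient safety and checking it costs little.

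**What to change.** The check should come before the wording, because the article does not give the appetite threshold and a sentence written first could be false.

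1. Check how the prostate app is configured for appetite.
2. If it uses a distress-only threshold, state that threshold in Digital nurse-led support. If the level is the highest one, this would do: *Appetite has no frequency question; an appetite alert is sent when distress is rated at the highest level.* If another level is used, name that level instead.
3. If the two-condition rule was programmed for appetite, set appetite to alert on *very distressing* alone, review the stored appetite reports at that level in the prostate intervention arm, and report the change and its date with the results.

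Cost: one configuration check and one sentence. Only if the check fails are an app correction, a query of stored reports and a note in the trial report also needed.

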### Outcomes

#### Acceptability and feasibility

To assess acceptability and feasibility, the participants in the intervention group and the study nurses will be interviewed about their experience of using Interaktor and the health dialogues. Furthermore, field notes with reflections from the health dialogues will be taken by study nurses. Objective measures will be extracted from the logged data in the app, that is, the number of reports (adherence) and self-care advice viewings. After the intervention has ended (at 6 months), the patients are surveyed via a questionnaire including the Acceptability E-scale^41^ and two selected items from the System Usability Scale.^42^ The composed questionnaire assesses ease of use, understandability, enjoyability, helpfulness, time required and overall satisfaction. To evaluate the feasibility of a future trial methodology, enrolment, recruitment and withdrawal rates will be documented. Other feasibility measures include completion rates and missing data in each study questionnaire.

#### Potential effect outcomes

To evaluate the potential effects of the intervention and obtain estimates for a future full-scale trial, outcomes are collected through self-reported standardised and validated questionnaires at baseline, and at 3, 6, 12, 18 and 24 months after intervention has started. HRQoL and symptom distress are assessed by the European Organisation for the Research and Treatment of Cancer Quality of Life Questionnaire EORTC-QLC-C30^43^ including disease-specific modules QLQ-PR25,^44^ QLQ- BR45^45^ and EQ-5d-5L^46^; the Patient Activation Measure for knowledge, skills, beliefs and confidence of managing health and healthcare^47^; the Sense of Coherence Scale-13, which measures overall coping ability^48^ and communicative and critical health literacy (5-items).^49^ The quantitative data will be triangulated with interview data from patients to explore perceptions regarding the effects of the intervention.

Medical data will be obtained from patients’ medical records. Demographic data (age, education, marital/civil status, having children at home, employment status, sickness absence) and comorbidity are self-reported. For the data measurement plan, see table 1.

#### Data management and blinding

All data is securely stored in line with the university regulations. Logged data for primary outcomes is retrieved on the university server where the Interaktor system is hosted. The secondary outcomes are collected through self-reported questionnaires at baseline, and at 3, 6, 12, 18 and 24 months after the intervention has started. The participants receive postal questionnaires at all six time points and reminders if not returned after 2 weeks. Patients are not blinded regarding treatment allocation as they are randomised in accordance with allocation to a PCC. The researchers will be blinded at data entry and when analysing coded patient-reported data.^50^ To maintain blindness, a separate data sheet of the outcome measures will be generated without a record or group I.D.

### Sample size

We adopted a sample size calculation for pilot randomised trials using a CI approach.^51^ To evaluate the potential effect of the intervention as compared with the control, and assuming a medium standardised effect size (0.5), 12 participants are required in each group with 80% one-sided CI. The question ‘overall satisfaction with the system’ in the Acceptability E-scale was chosen as a primary measure of acceptability for the sample size calculation. Aiming for the intervention to be acceptable to 70% of the participants with 20% precision (at least 50% were satisfied to use the intervention), 18 participants are required in the intervention arm. With an estimation of a 10% dropout, the total sample size of 20 participants in each study arm for each respective study group was considered appropriate.

### Analyses methods

Descriptive statistics will be used to analyse logged data from the use of the app, and descriptive qualitative analyses will be used for interview data. For the comparison of the potential effect measures between the groups, inferential and comparative statistical analyses appropriate for data level and distribution will be used, and mixed methods analysis will be applied to integrate quantitative and qualitative data.^52^

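### Primary care centres are randomised in five matched pairs, but the sample size makes no allowance for clustering and the analysis text does not commit to accounting for centre or pair

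*Protocol article*

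**What the plan says.** Under Study design, the protocol article explains that the intervention involves a whole PCC and that clusters are randomised to avoid spill-over. "Five pairs of PCC were matched to the CNI and the size of the PCC", and then "a randomisation through sealed envelopes allocated the PCC to either intervention or control in each pair". That makes five PCCs per arm.

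Under Sample size, two calculations are given. For the effect, "12 participants are required in each group with 80% one-sided CI". For acceptability: "Aiming for the intervention to be acceptable to 70% of the participants with 20% precision", from which "18 participants are required in the intervention arm". A 10% dropout allowance then leads to 20 per arm in each of the two trials. The section gives no ICC, design effect, number of PCCs or patients per PCC.

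Under Analyses methods, the comparison of potential effects is described in one clause: "inferential and comparative statistical analyses appropriate for data level and distribution will be used". No test or model is named.

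Data management and blinding adds that the analysis sheet will carry no record or group identifier. It does not say whether a PCC or pair code is kept.

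**The concern.** Patients in one intervention PCC have their health dialogues with a study nurse employed at that PCC, and they come from one catchment area. Their satisfaction, and to some degree their outcomes, can be expected to resemble each other. Eighteen such patients carry less information than 18 independent ones, so the precision claimed for acceptability, which is the figure that sets the sample size, is better than the design can deliver.

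The between-arm comparisons raise a related problem. The criteria given for choosing an analysis can be met by a test that treats each patient as a separate randomised unit. The article calls these comparisons inferential, and Potential effect outcomes says that they are to supply estimates for a full-scale trial. An interval that ignores the PCC would pass its error on to the planning of that trial.

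**Working it through.** **Inputs from the protocol article.** 5 PCCs per arm; 70% acceptability with 20 points of precision; 18 evaluable; 10% dropout; 20 recruited per arm.

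**Assumptions.** The ICC is not given; I use 0.01, 0.05 and 0.10. Patients are spread evenly over PCCs. The confidence level for acceptability is not stated; I use 95%.

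**1. Reproducing the plan's figure.**
- The Agresti-Coull half-width is z·√(p̃(1−p̃)/ñ), with ñ = n + z² and p̃ = (np + z²/2)/ñ. At p = 0.70 and z = 1.96, n = 17 gives 0.203 and n = 18 gives 0.198, so 18 is the first n within 0.20.
- The simple Wald formula gives 0.21·(1.96/0.20)² = 20.2, or 21, and does not match.
- Dropout: 18/0.9 = 20 exactly.
- The stated figure therefore reproduces with independent patients and a design effect of 1. The 12 per group for the effect is smaller and does not set the final number.

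**2. Acceptability with clustering.** Evaluable patients per PCC: 18/5 = 3.6. Design effect = 1 + (3.6 − 1)·ICC. Effective n = 18/design effect.

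| ICC | Design effect | Effective n | 95% half-width (Agresti-Coull) |
|---|---|---|---|
| 0 | 1.00 | 18.0 | 0.198 |
| 0.01 | 1.026 | 17.5 | 0.200 |
| 0.05 | 1.13 | 15.9 | 0.209 |
| 0.10 | 1.26 | 14.3 | 0.218 |

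**3. What it would take to keep 18 effective patients.** With 5 PCCs fixed, n = 18(1 − ICC)/(1 − 18·ICC/5). This is 18.5, 20.9 and 25.3, so 19, 21 and 26 evaluable. Dividing by 0.9 gives 22, 24 and 29 recruited, against 20.

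**4. Between-arm comparison if PCC were ignored.** With 20/5 = 4 per PCC, the design effect is 1 + 3·ICC = 1.03, 1.15 and 1.30. The true standard error exceeds the one reported by √1.03 = 1.01, √1.15 = 1.07 and √1.30 = 1.14.

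Simulating a plain two-sample t-test at nominal 5%, with no true effect, equal PCC sizes and no matching effect, gives rejection rates of about 5%, 7% and 9%.

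Few PCCs matter as well. Ten PCCs leave 8 degrees of freedom, where 40 patients would leave 38. At ICC 0.05 the 95% interval should be wider by √1.15 × t(8)/t(38) = 1.072 × 2.306/2.024 = 1.22. Most of that is the degrees of freedom: 2.306/2.024 = 1.14.

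**The case against.** A reader might infer that the stated analysis treats patients as independent and that its intervals will be too narrow. The article does not say so. It names no test. It is a condensed account, and the choice of model may properly sit in a full protocol or analysis plan that is not shown. This objection stands, so the analysis part of the point is conditional. What remains is that the one selection rule the article does state is silent on the unit of randomisation.

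The direction is not certain either. Ignoring an effective matching widens intervals, which works against the effect of ignoring PCC. Larger figures can be produced, but they are upper-end cases:
- Type I error near 11% needs ICC 0.10 together with invented, uneven PCC sizes.
- An interval 1.47 times as wide (4 degrees of freedom, ICC 0.05) credits matching with no gain.
- The smallest two-sided p-value of 2/2⁵ = 0.0625 applies only to a paired randomisation test; a mixed model is not bound by it.

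The shared nurse exists only in intervention PCCs, so that mechanism does not justify the same design effect in control PCCs. The effective sample sizes in the table are accordingly for the intervention arm, where acceptability is measured.

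Finally, Potential benefits and limitations says the study is not powered to test efficacy. That lowers the stakes, but it does not excuse a precision statement that leaves out the design. The sample size section is a finished calculation, not one deferred to another document.

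**Conclusion.** The sample size is wrong as written for this design: it rests on independent-patient formulas although PCCs are randomised, and the stated precision is not met under the assumed ICCs. The shortfall is small to moderate: effective n of about 17.5 down to 14.3 against 18, and a half-width of about 0.20–0.22 against 0.198. At ICC 0.01 it is negligible. These figures rest on an assumed ICC of 0.01 to 0.10, an even spread over PCCs and a 95% level.

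For the between-arm comparisons, the supportable statement is that the article does not commit to accounting for PCC or pair. Intervals will be too narrow only if PCC is ignored and the ICC is positive, and less so if the matching is effective. Likewise, a blinded sheet without PCC codes would prevent a clustered analysis from that sheet, but the text does not settle whether the codes are dropped. For a pilot centred on acceptability and feasibility, this should be fixed; it does not invalidate the trial.

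**What to change.** - **Sample size:** state 5 PCCs per arm, about 4 recruited (3.6 evaluable) patients per PCC, an assumed ICC range, and the resulting effective n and half-width. Keep 20 per arm and accept the lower precision openly. Holding the 18-patient target instead would need 22 to 29 per arm over the assumed range.
- **Analyses methods:** state that between-arm comparisons account for PCC and matched pair with small-sample degrees of freedom, by a mixed model or a paired PCC-level analysis. Report estimates with confidence intervals, and give acceptability an interval that allows for clustering by PCC.
- **Data management and blinding:** state that masked PCC and pair codes stay in the analysis sheet, without revealing the arm.

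The cost is wording and model code, with no added patients. The downside is wider, less favourable intervals.
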